### 3.6 Compliance with Study Intervention

Issues with patient compliance with the study intervention are not expected given that the graft procedure for the study product will be completed by the Investigator/surgeon. Once the patient has been discharged from hospital post-operatively, compliance issues may arise.

In conclusion, compliance issues that could affect the primary endpoint (i.e. compliance with treatment and during the early follow-up period) are not anticipated. However, compliance issues could also arise later in the treatment course if the patient does not fulfil their outpatient follow-up requirements, which could potentially influence the secondary and exploratory endpoints.

It is possible that the issue arises that a minor patient declines further participation by showing signs of resistance. In such a case, it is the responsibility of the Investigator that the minor patient will be excluded (in The Netherlands in accordance with the NVK behavioural code).

### 3.7 Concomitant Medication

Documentation of concomitant medication use will be recorded at each visit.

All routine drugs administered following skin defect closure by split-thickness skin grafting, including drugs against pruritus, local ointments, local antibiotic ointments, routine dressing devices etc. are allowed.

All concomitant and/or rescue treatments with the exception of standard perioperative medication have to be documented in the eCRF. The medication listed in Table 3 will not be documented in the eCRF (only in the patient record).

**Table 3:** Standard perioperative medication not to be documented in eCRF

| Active component                                                                         | Active component |
|------------------------------------------------------------------------------------------|------------------|
| Midazolam                                                                                | NaCl 0,9%        |
| Propofol                                                                                 | Ephedrine        |
| Alfentanil                                                                               | Ondansetron      |
| Fentanyl                                                                                 | Paracetamol      |
| Atracurium                                                                               | Sevoflurane      |
| Ringeracetat-Glc. 1%                                                                     | Atropine         |
| Ketamine                                                                                 | Droperidol       |
| Remifentanyl                                                                             | Nalbuphin        |
| TLA-Solution (1000ml NaCl 0,9% + 1ml Adrenalin 0,1% + 6ml NaBic 8,4% + 50ml Xylonest 1%) |                  |

#### 3.7.1 Prohibited Concomitant Medication

There are no known prohibited medications.

#### 3.7.2 Allowed Concomitant Medication

All medications will be accepted.

#### 3.7.3 Concomitant Medication to be used with Caution

There are no known medications to be used with caution.

#### 3.7.4 Allowed Dressing

Mepilex Ag is the recommended dressing, especially until the first dressing change. However, all dressings commonly used with STSG are allowed.

## 4. Selection of Study Population

### 4.1 Inclusion Criteria

- Age:  $\geq 12$  years of age
- Deep partial thickness and/or full-thickness burns requiring surgical wound coverage
- Expected that  $\geq 90$  cm^2 of wound (not counting head and neck area for study patients in The Netherlands) will remain open at 4 weeks post burn despite proceeding with treatment in accordance with the standard of care.  $> 20\%$  TBSA burns can be taken as guideline, but TBSA is not an inclusion criterion.
- Signed Informed consent from the patient or the parents/legally authorized representative

### 4.2 Exclusion Criteria

- Patients tested positive for HBV, HCV, syphilis or HIV
- Patients with known underlying or concomitant medical conditions that may interfere with normal wound healing (e.g. systemic skin and connective tissue diseases, any kind of congenital defect of metabolism including insulin-dependent diabetes mellitus, Cushing syndrome or disease, scurvy, chronic hypothyroidism, congenital or acquired immunosuppressive condition, chronic renal failure, or chronic hepatic dysfunction (Child-Pugh class B or C), severe malnutrition, or other concomitant illness which, in the opinion of the Investigator, has the potential to significantly delay wound healing)
- Severe drug and alcohol abuse
- Pre-existing coagulation disorders as defined by INR outside its normal value, PTT  $> \text{ULN}$  and fibrinogen  $< \text{LLN}$  prior to the current hospital admission and / or at the Investigator's discretion
- Patients with known allergies to amphotericin B, gentamicin, penicillin, streptomycin, or bovine collagen
- Previous enrolment of the patient into the current phase II study
- Participation of the patient in another study with conflicting endpoints within 30 days preceding and during the present study
- Patients expected not to comply with the study protocol (including patients with severe cognitive dysfunction/impairment and severe psychiatric disorders)
- Suspicion of non-accidental injury
- Pregnant or breast feeding females
- Intention to become pregnant during the clinical course of the study (12 months)
- Wounds in the head and neck area as study target area (only applicable for study patients in The Netherlands)
- Enrolment of the Investigator, his/her family members, employees, and other dependent persons

#### 4.2.1 Contraception Methods

As to ensure appropriate contraception measures and avoid pregnancy in females post menarche, the Investigators are required to instruct the patients on the consistent and correct use of the chosen contraception at each visit during the clinical phase of the study (until visit 10). In addition, the Investigator instructs the patient to call immediately if the selected birth control method is discontinued or if pregnancy is known or suspected.

Highly effective methods of contraception are those that, alone or in combination, result in a failure rate of less than 1% per year when used consistently and correctly and include:

- Established use of oral, inserted, injected or implanted hormonal methods of contraception are allowed provided the patient remains on the same treatment throughout the clinical phase of the study (until visit 10) and has been using that hormonal contraceptive for an adequate period of time to ensure effectiveness.
- Correctly placed copper containing intrauterine device.
- Male condom or female condom used WITH a spermicide (this can be foam, gel, film, cream, suppository).
- Male sterilisation with appropriately confirmed absence of sperm in the post-vasectomy ejaculate.
- Bilateral tubal ligation or bilateral salpingectomy.

### **4.3 Criteria for Withdrawal / Discontinuation of Patients**

#### **4.3.1 Early Withdrawal of Patients**

The patient himself/herself and the patient's parents/legally authorized representative have the right to withdraw the patient from the study at any time and for any reason.

#### **4.3.2 Criteria for Early Withdrawal of Patients by Investigator**

In case of matching one of the following criteria during the study, the patient is withdrawn from the study by the Investigator:

- The initial evaluation at the time of the biopsy is not confirmed in the further course of treatment and the new evaluation dictates that no skin grafting is necessary.
- Presence of infection at the study site(s), as per the clinical evaluation of an Investigator with expertise in burn surgery, which has not resolved by the time of the grafting procedure.
- Clear evidence of poor compliance of patient (e.g. not attending scheduled visits more than once without notification, not following medical advice concerning mobilization etc.). However, these patients will be followed up for safety purposes as per the schedule.
- Newly diagnosed or reported underlying medical conditions (up to the point of grafting) that meet the exclusion criteria (e.g. newly diagnosed diabetes mellitus during the study).
- Severe graft damage during transport from the manufacturing site to the operating room. Defect coverage is then performed in accordance with the standard of care. (The patient does not need to be withdrawn from the study if the Investigator and study patient agree to continue the study and it is expected that  $\geq 90$  cm^2 of wound (not counting head and neck area for study patients in The Netherlands) will remain open when newly produced IMP is ready, despite proceeding with treatment in accordance with the standard of care. IMP will then be produced from previously harvested cells or from a new biopsy.)
- Serious deterioration of the patient's general health status leading to switch to palliative care (up to the point of grafting).
- Patient's ineligibility for the study after biopsy due to poor cell numbers or vitality of the cells during the manufacturing process of the graft, and the patient and/or parents/legally authorized representative refuses to consent to have a second biopsy carried out for a second manufacturing process.
- Ineligibility of the graft for grafting (no release of the final product) as determined at the manufacturer's discretion and/or Investigator's discretion, and impossibility to manufacture a new graft either by absence of cryopreserved cellular stock or absence

of consent from the patient and/ legally authorized representative for a new biopsy. Graft manufacturing failure as described in this chapter will be documented in the eCRF.

- Patients with 100% loss of the grafted EHSG-KF will be withdrawn from the study following the Safety Follow-up at 1 year  $\pm$  30 days (visit 10).
- Minor patients show resistance to study participation, (in The Netherlands in accordance with the NVK behavioural code).

Furthermore, should a study patient experience an AE or SAE that meets the following criteria, the patient may be immediately discontinued from the study.

- Any AE or SAE in the judgment of the Investigator or the patient, justifies withdrawal due to its severity, its nature, or requirement for treatment, regardless of the causal relationship to the IMP
- Clinically relevant test procedure results which endanger the patient

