#### **4.3.3 Replacement of Patients**

The following points describe the procedure of replacement/enrolment of patients:

- Drop-out prior to grafting: Patient is replaced
- Drop-out after grafting: Patient is not replaced

Patients will continue to be enrolled in the study until 12 patients were evaluated for primary endpoint (visit 6) (see chapter 10.2).

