## 9. Safety

All adverse events (AEs) and all serious adverse events (SAEs) occurring from visit 2 (Biopsy) until visit 12 (3 years post-grafting) will be collected. They will be fully investigated and documented in source documents and eCRF.

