### 10.2 Determination of Sample Size

The primary endpoint (i.e. the ratio of covered surface area to biopsy site / donor site surface area at 4 weeks post grafting) will be analysed after a logarithmic transformation and the treatment effect estimate will be expressed as a percentage of additional coverage obtained with EHSG-KF comparatively to STSG.

Published data of cultured skin substitutes in a series of 10 patients (Boyce 1995, Table 11) show on the logarithm of the ratio of covered surface area to biopsy site surface area (also named expansion ratio) at 1 month post grafting a standard deviation of 0.97 with a mean of 1.98 (corresponding to a geometric mean of 7.24 on the original scale). Data from the EHSG-KF Phase I clinical trial (excluding one patient with 100% graft loss attributable to patient noncompliance and manipulation of the dressing post-operatively) show on the logarithm of the ratio of covered surface area to biopsy site surface area at 3 weeks post grafting a standard deviation of 0.99 with a mean of 1.80 (corresponding to a geometric mean of 6.05 on the original scale). A standard deviation of 1.00 will be assumed for the difference (on the logarithmic scale) between the two treatments, corresponding, for instance, to a common standard deviation of 1.00 on each treatment site with a correlation between sites of 0.50.

The ratio of covered surface area to biopsy site / donor site surface area at 4 weeks post grafting is expected to be at least 145% higher on EHSG-KF than on STSG (corresponding, for instance, to ratios of 7.35 and 3.00, respectively).

- Assuming a standard deviation of 1.00 for the paired difference between the 2 log(ratios), a sample size of 12 evaluable patients would be required in order to achieve a power of 80% to detect a treatment effect corresponding to an increase of 145% with EHSG-KF (i.e. to a difference of 0.90 on a logarithmic scale) when using a one-sample t-test at two-sided significance level of 5%.  
A claim of study success will be made when the two-sided test passes the significance level of 0.05.
- All secondary endpoints will be tested in a strictly exploratory fashion only.

**Table 11:** Criteria for sample size determination

| Criteria                                                                                   | Value |
|--------------------------------------------------------------------------------------------|-------|

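### Withdrawal rules that act after grafting can leave a patient without a visit 6 ratio, and they remove complete EHSG-KF failures from the visit 11 and 12 comparisons and adverse event collection

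*Protocol*

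**What the plan says.** Section 4.3.2 lists criteria on which the investigator withdraws the patient.

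- **Poor compliance.** The criterion is "Clear evidence of poor compliance of patient (e.g. not attending scheduled visits more than once without notification, not following medical advice concerning mobilization etc". The next sentence keeps these patients on the visit schedule, for safety purposes.
- **Total loss of the experimental graft.** "Patients with 100% loss of the grafted EHSG-KF will be withdrawn from the study following the Safety Follow-up at 1 year", which is visit 10. There is no corresponding criterion for total loss of the STSG.

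Section 4.4 retains and analyses data up to withdrawal. The examination it defines for early leavers consists of a physical examination, vital signs and routine laboratory tests. Patients leaving after visit 10 because of total graft loss are excused even from that.

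Section 4.3.3 says "Drop-out after grafting: Patient is not replaced" and also "Patients will continue to be enrolled in the study until 12 patients were evaluated for primary endpoint (visit 6").

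Section 9 states that all adverse events "occurring from visit 2 (Biopsy) until visit 12 (3 years post-grafting) will be collected", and section 8.2.8 makes the same period a secondary endpoint. Section 10.3.1 defines the mITT as treated patients with at least one post-surgical measurement, analysed as randomised. Section 10.3.2 tests the paired log-ratio difference at 4 weeks.

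**The concern.** The intervention is a single operation at visit 3. Withdrawal after that date cannot change exposure; it can only stop data. If the reason for stopping relates to how the experimental graft fared, the missing values are informative.

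Two things are at stake. The first is the primary comparison, which rests on 12 evaluable patients, so that one missing or included failure can matter. The second is the long-term record. The 2- and 3-year scar, colour and growth comparisons would describe only patients whose EHSG-KF did not fail completely. Patients exposed to the product would also lose routine adverse event collection over the last two years, although section 1.3.2 says a tumorigenicity risk has not been definitively excluded.

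**Working it through.** **1. The plan's own figure.** Section 10.2 assumes "a difference of 0.90 on a logarithmic scale", SD 1.00 for the paired difference, two-sided 5% and 80% power. Exact one-sample t-test power (noncentral t) is 76.7% for n = 11 and 81.0% for n = 12. The stated 12 is reproduced. The synopsis figure of 15 corresponds to 12/(1 − 0.20).

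**2. Can the compliance rule act between visits 3 and 6?** The criteria on newly diagnosed conditions and on serious deterioration are both limited to the time before grafting. Section 9.5 keeps in the study patients who become pregnant after visit 3. The compliance criterion has no such limit. Missing visits 4 and 5 without notice, or disregarding mobilisation advice after surgery, would meet it before visit 6.

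**3. Is the visit 6 ratio then secured?**

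- Follow-up after a compliance withdrawal is for safety.
- The early-leaver examination (4.4, 8.2.13) contains no planimetry.
- Data are kept up to withdrawal, which does not cover a later visit 6.
- The mITT retains the patient, but the paired test needs a visit 6 value.

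So the text neither requires nor forbids the measurement.

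**4. What the total-loss rule removes.** Withdrawal follows visit 10, so visit 6 (primary), visit 8 (first secondary) and visit 10 (main secondary scar endpoints) remain due. Lost for both areas are Cutometer, POSAS and colour at visits 11 and 12, growth from visit 10 to visit 12, and routine adverse event collection after visit 10.

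**5. How much one patient could matter (illustration).** Take 11 patients with mean exactly 0.90 and SD exactly 1.00: t = 0.90 × √11 = 2.98, p = 0.014, an increase of exp(0.90) − 1 = 146%. Add one near-total EHSG-KF loss with a 4 cm² biopsy, a control ratio of 3 and an assumed residual covered area a. The added difference is ln(a/4) − ln 3, and the new mean is (11 × 0.90 + difference)/12.

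| a (cm²) | Difference | Mean of 12 | Increase | t-test p | Wilcoxon p |
|---|---|---|---|---|---|
| 1.0 | −2.48 | 0.62 | 86% | 0.15 | 0.11 |
| 0.5 | −3.18 | 0.56 | 75% | 0.23 | 0.13 |
| 0.1 | −4.79 | 0.43 | 53% | 0.45 | 0.13 |

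Without that patient the Wilcoxon p is 0.019. A positive a is needed because the logarithm of a zero ratio is undefined; that is a separate matter.

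**6. How often total loss might occur.** Section 1.1.2 reports one total loss in 10 phase I patients. At that rate 12 × 0.1 = 1.2 to 15 × 0.1 = 1.5 are expected here. The exact 95% interval for 1/10 runs from about 0.3% to 45%, so the upper end would be 12 × 0.45 = 5.4 to 15 × 0.45 = 6.75 patients. This bears on the visit 11 and 12 rule. It is not a rate of compliance withdrawal before visit 6, and the protocol gives none.

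**7. Section 4.3.3.** A patient lost between grafting and visit 6 is not replaced under one sentence, yet is made up for under the other, since enrolment runs to 12 evaluated. With 15 randomised, 15 − 12 = 3 such losses are covered. For a fourth the text does not say which sentence governs.

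**The case against.** A reader might infer that losses linked to the experimental graft leave the primary analysis. The documents do not support that. The only rule on graft loss keeps total failures in for visits 6, 8 and 10. The compliance rule acts on the patient, and so on both areas; it names neither EHSG-KF nor a time before visit 6. The mITT already keeps treated patients, and major deviations are excluded only from the supportive per-protocol set. Section 3.6 does not anticipate compliance problems that affect the primary endpoint.

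The phase I precedent also cuts both ways. Section 10.2 attributes the total loss to noncompliance and leaves it out of the planning figures. Section 1.1.2, however, counts it as 0% in the overall graft take (70.6 × 9/10 = 63.5), and nowhere is that patient said to have been withdrawn. A reader might also convert 1/10 into a 72% chance of at least one case in 12 (1 − 0.9¹²). That is the chance of a total loss, not of a withdrawal before visit 6, and on the interval above it runs from about 3% to over 99%.

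On the long-term side, the visit 11 and 12 efficacy endpoints are exploratory. After total loss no EHSG-KF scar remains, and the area may have been closed by other means. Safety is only partly cut: ongoing SAEs are followed (4.4), and related SAEs learned of later must be reported (9.4.1). Section 4.3.3 can be read as no one-for-one replacement, with recruitment continuing to 12 evaluable patients.

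All of this stands and limits the point. It does not supply the missing instruction to measure visit 6 after a compliance withdrawal. Nor does it explain why only total EHSG-KF loss ends follow-up, or reconcile that rule with adverse event collection to visit 12.

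**Conclusion.** Two defects hold.

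1. **Primary endpoint: a gap, not a prescribed exclusion.** Mandatory withdrawal for poor compliance extends past grafting and secures only safety follow-up, so the visit 6 ratio may be missing for a patient who still attends. Whether such withdrawals follow EHSG-KF loss is an inference from one phase I case. Its frequency is unknown, so no expected bias can be stated. The illustration shows only that a single near-total loss, present or absent, could decide the success claim, under the planning values and the assumed residual areas.

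2. **Long-term follow-up: stated outright.** The total-loss rule depends on the experimental outcome and is one-sided. It conditions the exploratory visit 11 and 12 comparisons on EHSG-KF not having failed completely, and it conflicts with sections 8.2.8 and 9 on adverse events. At the assumed phase I rate it touches one or two patients, with wide uncertainty.

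The two sentences in section 4.3.3 are a wording conflict and no source of bias in themselves. Overall this is an inexpensive improvement that should be made; it does not invalidate the primary analysis.

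**What to change.** - **Section 4.3.2:** state that, once the graft has been applied, poor compliance or total graft loss does not end study assessments unless the patient withdraws consent.
- **Visits 6 and 8:** for patients with poor compliance after grafting, collect planimetry and epithelialisation at the visits they already attend, and analyse them in the mITT as randomised.
- **Visits 11 and 12:** keep total-loss patients for adverse events and for both study areas, analysed as randomised. Align section 4.4 accordingly.
- **Section 4.3.3:** reword so that the two sentences agree, for example: no one-for-one replacement after grafting, with recruitment continuing until 12 patients have the visit 6 endpoint. State whether 15 randomised patients is a ceiling.

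These changes concern data collection and leave clinical care as it is. The cost is a small amendment, assessments at visits already scheduled, and at most two additional long-term visits per affected patient, for one or two patients at the phase I rate.

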#### **4.3.3 Replacement of Patients**

The following points describe the procedure of replacement/enrolment of patients:

- Drop-out prior to grafting: Patient is replaced
- Drop-out after grafting: Patient is not replaced

Patients will continue to be enrolled in the study until 12 patients were evaluated for primary endpoint (visit 6) (see chapter 10.2).

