| Study
Procedure              | 
Invasive procedures:
 
 
• Biopsy Nr. 1: mandatory biopsy, required for EHSG-KF production
 
• Biopsy Nr. 2-5: facultative biopsies before and after debridement for histological examination of the wound bed
 
• Blood samples for screening lab test
 
• Blood samples for routine lab test
 
• Grafting of EHSG-KF / STSG
 
 
Optional Invasive procedures:
 
 
• Optional biopsy Nr. 6-9: optional biopsy for routine histology and immunohistochemistry at visits 8 and 10
 
 
Non Invasive procedures:
 
 
• Physical examinations
 
• Elasticity assessment of the skin
 
• Colour assessment of the skin
 
• Photographic documentation of study areas
 
• Questionnaires 
 
○ POSAS for all patients
 
○ EQ-5D and BSHS-B for patients <math>\geq 18</math> years
 
○ EQ-5DY and PedsQL for patients <math>< 18</math> years
 
 
 
 |
| Statistical
Considerations:  | 
 
• The primary endpoint (ratio of covered area to biopsy site / donor site surface area at 4 weeks post-grafting) will be analysed after logarithmic transformation by a one sample t-test at significance level of 5%
 
• Assuming a standard deviation of 1.00 for the paired difference between the 2 log (ratios), a sample size of 12 evaluable patients would be required in order to achieve a power of 80% to detect a treatment effect corresponding to an increase of 145% with EHSG-KF (i.e. to a difference of 0.90 on a logarithmic scale) when using a one-sample t-test at two-sided significance level of 5%. This calculated number may be inflated to 15 randomised patients in order to cover for possible drop-outs before the assessment of the primary endpoint.
 
                                                                                                                                                                                                                                                                                              |

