#### 10.1.3 Interim analysis

In the interest of the development of the product, the Sponsor might extract data by means of an interim analysis from the first 12 patients who received denovoSkin™ to perform a submission to a regulatory agency for a request of designation such as for example the priority Medicines scheme (PRIME) in Europe and the Regenerative Medicine Advanced Therapy (RMAT) in the US. This will not interfere with the conduct of the study for the following up to 3 patients. The interim analysis will be done on a database that has been cleaned up to that the month 3 visit (V6) and will be performed on part of the efficacy and safety endpoints. The interim analysis will include the statistical analysis on the primary efficacy endpoint (final results will not change) and only descriptive statistics on the other endpoints, described in an interim-specific SAP (statistical analysis plan). A correction for multiple comparisons is considered not needed.

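### Section 4.3.3 gives opposite enrolment instructions for a patient lost between grafting and visit 6, and the protocol does not fix whether patients 13 to 15 are enrolled or enter the final primary test

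*Protocol*

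**What the plan says.** Section 4.3.3 has two bullets and a closing sentence. Patients lost before grafting are replaced. For those lost later the bullet reads "Drop-out after grafting: Patient is not replaced". The closing sentence reads "Patients will continue to be enrolled in the study until 12 patients were evaluated for primary endpoint (visit 6" and refers the reader to section 10.2.

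Section 10.2 sets the target: "a sample size of 12 evaluable patients would be required in order to achieve a power of 80" per cent. It mentions neither 15 patients nor drop-outs. The allowance is in the synopsis: "This calculated number may be inflated to 15 randomised patients in order to cover for possible drop-outs before the assessment of the primary endpoint".

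Section 10.1.3 allows an interim analysis, including the primary test, on the first 12 patients who received the product. It says of the remainder: "This will not interfere with the conduct of the study for the following up to 3 patients". In parentheses it adds that the final primary result will be unchanged, and it judges a multiplicity correction unnecessary.

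Section 10.3.1 defines the mITT, the primary analysis population, as all randomised and treated patients with at least one measurement after surgery.

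**The concern.** The only grafted patients whose loss costs primary-endpoint data are those lost between day 0 and visit 6. For exactly these patients the bullet and the closing sentence of 4.3.3 point in opposite directions. For losses after visit 6 they agree. This is an instruction about enrolment, so it belongs in the protocol and is not a detail to leave for the SAP.

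Two things are at stake. The power statement is conditional on 12 evaluable patients, and strict use of the no-replacement line could leave fewer. The final number is also open between 12 and 15. The trial is open label and the sponsor may see the primary test on the first 12 treated, so the rule deciding whether later patients are enrolled and counted should be settled beforehand.

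**Working it through.** **1. Reproduce the planned sample size.** Inputs, all from section 10.2:

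- Test: "one-sample t-test at two-sided significance level of 5" per cent.
- Effect: "to a difference of 0.90 on a logarithmic scale", for an increase of 145% (ln 2.45 = 0.896).
- Spread: "Assuming a standard deviation of 1.00 for the paired difference between the 2 log(ratios".
- Each patient supplies one pair, so n is the number of patients with both sites assessed at visit 6.

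Exact power uses the noncentral t distribution with df = n − 1 and noncentrality 0.90 × √n / 1.00:

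power = P(|T| > t(0.975, n − 1)).

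For n = 12, the noncentrality is 0.90 × 3.464 = 3.118, the critical value is t(0.975, 11) = 2.201, and power is 0.810. For n = 11 it is 0.767. The smallest n reaching 0.80 is therefore 12, as the protocol states. With ln 2.45 in place of 0.90, power at n = 12 is 0.806.

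**2. Reproduce the allowance.** 12 / 15 = 0.80, so 15 randomised covers a 20% loss, that is 3 patients. Twelve counts evaluable patients and 15 counts randomised patients.

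**3. Power by number evaluated at visit 6.**

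| Evaluated | Power |
|---|---|
| 9 | 65.9% |
| 10 | 71.7% |
| 11 | 76.7% |
| 12 | 81.0% |
| 13 | 84.5% |
| 14 | 87.5% |
| 15 | 89.9% |

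**4. Apply each reading of the text.**

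- Enrol until 12 are evaluated: at least 12, so power is at least 81.0%.
- Randomise 15, replace nobody lost after grafting, lose 0 to 3 before visit 6: 12 to 15 evaluated, 81.0% to 89.9%.
- Randomise 15, replace nobody, lose 4: 15 − 4 = 11 evaluated, 76.7%.
- Stop at 12 grafted and replace nobody: one loss gives 76.7%, two give 71.7%. No section states a stop at 12 grafted.

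The protocol gives no drop-out rate between grafting and visit 6, so the loss counts above are assumptions.

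**5. Which patients enter the primary test.** The milestone in 4.3.3 is 12 evaluated at visit 6, and in 10.1.3 it is 12 treated. Manufacturing takes about 26 to 32 days (section 3.3) and visit 6 comes 28 ± 3 days after grafting. Further patients can therefore be in manufacturing, or already grafted, when the twelfth is evaluated. The protocol does not say what happens to them. If they are grafted and measured once, 10.3.1 puts them in the mITT. The primary estimate and p-value can then differ from those on the first 12, contrary to the remark in 10.1.3.

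**The case against.** Section 4.3.3 can be read coherently. The bullets may concern a patient's place: someone lost before grafting is substituted, while a grafted patient keeps the place and stays in the analysis sets. The closing sentence then says when enrolment ends, and the synopsis says early losses are covered by over-enrolment and not by one-for-one replacement. On that reading the trial reaches 12 evaluable. The affected group is also narrow. Section 3.6 anticipates no compliance problems that affect the primary endpoint, and under 4.3.2 a patient with complete graft loss is withdrawn only after visit 10.

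Much of this stands. It shows that the intention was probably 12 evaluable. It does not remove the conflict, because it leaves the no-replacement bullet without effect for losses before visit 6, and the bullet carries no such limit.

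A reader might infer more than the documents support:

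- That 12 and 15 are rival sample sizes. They are an evaluable target and an optional allowance for losses.
- That the 80% power is already compromised. That needs fewer than 12 evaluated, which the closing sentence of 4.3.3 is written to prevent.
- That section 10.1.3 contradicts the enrolment rule by expecting more patients. Its wording permits zero, and it counts from 12 treated, not 12 evaluated.
- That the type I error is inflated. If success could be claimed at 12 or again at 15, all evaluable, each tested at an unadjusted 5%, a simulation of 1,000,000 null trials gives about 7.2%. The protocol does not say that success may be claimed at either test, so this shows why the rule should be fixed and is not a property of the plan.

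**Conclusion.** The point holds in a limited form. The unrestricted no-replacement bullet conflicts with the enrolment sentence for patients lost between grafting and visit 6. The sample-size calculation itself is sound. Under the stated effect of 0.90 and SD of 1.00, power is 81.0% at 12 evaluable and stays between 81.0% and 89.9% for 12 to 15. The shortfall, to 76.7% at 11 or 71.7% at 10, arises only if the bullet is followed literally and too few patients are evaluated.

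Separately, the final number is not fixed between 12 and 15, and the remark in 10.1.3 that the primary result is already final does not fit the mITT in 10.3.1 if later patients are grafted. In an open-label trial with a possible early primary test, both are worth settling in the protocol.

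**What to change.** 1. In 4.3.3, limit non-replacement to drop-outs after the visit 6 assessment.
2. In 4.3.3, the synopsis and 10.2, state one rule: enrolment ends when 12 patients have the visit 6 primary assessment. Describe 15 randomised as the planned drop-out allowance. It should not be a cap that overrides the 12 evaluable, because a hard cap would defeat that target once four patients were lost.
3. State that all mITT patients with a visit 6 assessment enter one final primary test, including any already in manufacturing or grafted when enrolment ends and assessed later.
4. In 10.1.3, use the same milestone. Replace the remark that the final result is unchanged with a statement that the claim of success rests on that single final test, so the number analysed cannot be chosen after results are seen.

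The cost is protocol wording. No patients are added within the planned allowance of 15. More than 15 would be needed only if over 3 of 15 were lost before visit 6, which the existing enrolment sentence already implies.
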